## Results and Discussion

### Characteristics of Bayesian stopping guideline for individual groups

The minimum number of failures required to satisfy the stopping criteria for the main monitoring beta (4.5, 0.5) prior and for each number of analysed patients is listed in Table 3. The probability of stopping a group is then the probability of observing the required number of failures in the group. When the true cure rate is 90%, the probability of incorrectly stopping a group is always less than 0.05 and this decreases as the true cure rate increases. It is expected from the specification of the stopping guideline that when the true cure rate is equal to the mean of the prior, the probability of stopping a group is 0.05, so the probability of incorrectly stopping a group is always maintained below the correct level. The calculated probability is not exactly 0.05 and differs depending on the number of patients analysed due to the discrete nature of the outcome.

**Table 3 Tab3:** Number of failures needed to stop a drug strategy group for each number of analysed patients

Analysed patients	Minimum number of observed failures needed to stop group^a^	Maximum probability of stopping group if true cure rate equals:		Minimum probability of stopping group if true cure rate equals:			
		90%	95%	90%	80%	70%	60%
3–7	3	0.026	0.004	0.001	0.008	0.027	0.064
8–13	4	0.034	0.003	0.005	0.056	0.194	0.406
14–20	5	0.043	0.003	0.009	0.130	0.416	0.721
21–26	6	0.040	0.002	0.014	0.231	0.637	0.904
27–33	7	0.042	0.001	0.015	0.287	0.744	0.958
34–39^b^	8	0.037	0.001	0.017	0.367	0.844	0.986
40–41^b^	8	0.048	0.001	0.042	0.563	0.945	0.998
42–48	9	0.046	0.001	0.021	0.469	0.920	0.997
49–55	10	0.044	0.0004	0.022	0.528	0.952	0.999
56–63	11	0.047	0.0003	0.021	0.580	0.971	1.000
64–71	12	0.048	0.0002	0.023	0.648	0.985	1.000
72–78	13	0.045	0.0001	0.025	0.705	0.993	1.000

Groups will recruit a minimum of 78 patients with 39 patients in each stratum if recruitment is not stopped into that group. If recruitment is stopped into one group, the maximum number of patients in each other group and the other stratum for that group will be higher

Maximum and minimum probabilities are for the range of analysed patients

^a^ More than 0.95 posterior probability of the true cure rate being less than 90% (Pr(true cure rate < 0.9|x) > 0.95, where x is the data currently observed, with the beta (4.5, 0.5) prior which has mean = 0.9 and variance = 0.015

^b^ These rows not pooled despite the same number of minimum failures to provide information about the fully recruited strata (*n* = 39)

For small numbers of analysed patients, a larger proportion of failures are required to stop a group, increasing from a minimum of 17% to 100% of those analysed; therefore, the probability of stopping a group incorrectly early in recruitment is also smaller as there is a smaller chance of observing greater proportions of failures regardless of the true cure rate. This protects against groups being stopped erroneously because of a high concentration of failures amongst the initial patients reaching EOT + 12, and if the two strata within a group share the same true cure rate, then it is unlikely that only one will reach the stopping threshold.

Groups with the lowest cure rates considered plausible (60%) are highly likely to reach the stopping criteria quickly (>90% chance of stopping after analysing 21–26 patients). Groups with moderately low cure rates (<80%) are also likely to be stopped before recruitment ends. However, groups with true cure rates slightly under 90% are unlikely to be stopped (results not shown). A low chance of stopping a group just below the target cure rate might be considered unacceptable in futility stopping guidelines in other situations, but the target of 90% is largely arbitrary and there may be interest in strategies that have a slightly lower cure rate if they are able to expand treatment access to difficult-to-reach populations. Increasing the probability of stopping groups with cure rates just below 90% would lead to a greater chance of incorrectly stopping groups with cure rates of more than 90% and it is considered more important to retain these than to stop groups with slightly lower cure rates. Additionally, any other stopping guideline would similarly be unable to discriminate between these cure rates without a very large sample size. The probability of incorrectly not stopping a group rapidly decreases as the true cure rate decreases.

The overall probability of stopping a group, and therefore making a correct decision or incorrect decision to stop recruitment into a group (again analogous to the frequentist concepts of power and type I error), shows results similar to those given above (Supplementary Table 1, Additional file 1). For cure rates of more than 90%, the probability of incorrectly stopping a group is always maintained less than 0.05, and for cure rates of less than 90%, there is a high probability of correctly stopping a group, and almost all groups are stopped when the true cure rate is not more than 70%. The probability of incorrectly not stopping groups with cure rates of about 80% is 12%, and for cure rates of 90%, a group is far more likely not to be stopped than correctly stopped. However, as described above, for our design this is not as much of a concern as it may be for other trial designs because the aim of the monitoring is to stop clearly inferior regimens rather than those close to the arbitrary 90% threshold.

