**Results:**

A beta (4.5, 0.5) prior for the true cure rate produces less than 0.05 probability of incorrectly stopping an individual randomly assigned group with a true cure rate of more than 90%. Groups with very low cure rates (<60%) are very likely (>0.9 probability) to stop after about 25% of patients are recruited. Groups with moderately low cure rates (80%) are likely to stop (0.7 probability) before overall recruitment finishes. Interim analyses 7, 10, 13 and 18 months after recruitment commences provide good probabilities of stopping inferior individual randomly assigned groups. For an overall true cure rate of 95%, power is more than 90% to confirm non-inferiority in the regimen and strategy comparisons, regardless of the control cure rate, and to detect a 5% absolute difference in the ribavirin comparison.

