### Monitoring

For the strategies to be viable outside the trial, first-line cure rates need to be high (>90%). The design of the trial therefore allows for failing groups to be stopped early at any time and subsequent patients to be randomly assigned to more successful groups. Individual performance of groups receiving shortening strategies will be monitored during recruitment by an independent DMC that will make decisions on whether a group should be stopped. Groups receiving standard 12-week treatment will not be monitored as this is the licensed duration with cure rates of more than 90% [28, 29]. Interim analyses will not be comparative as the aim of monitoring is not to find the best strategy but to find any strategy that meets a minimum acceptable cure rate that may also be non-inferior to standard treatment as different strategies may benefit different patient populations.

Analyses of cure rates will follow the Bayesian paradigm to allow the probability of the true cure rate being below different thresholds to be calculated: recruitment into a group will stop if there is a greater than 0.95 posterior probability of the true cure rate being less than 90% (Pr(true cure rate <0.9|x) >0.95, where x is the data currently observed). The primary monitoring is combined across genotypes; if the combined group reaches the stopping guideline, each genotype stratum will be tested separately and the DMC will have the discretion to stop only those strata reaching the stopping criteria. Differences in stopping groups across strata are likely to occur only when there are extreme differences in the cure rates between the strata, which is not expected, and so the operating characteristics of the trial are based on stopping combined strata only. If neither stratum reaches the stopping criteria despite the combined strata doing so, it will be at the discretion of the DMC whether to stop recruitment into the stratum or group.

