At interim analyses, there is greater uncertainty about the performance of the shortening strategies. Therefore, when the prior was determined, it was assumed that one strategy would fail completely such that all four groups receiving that strategy, of a total of 12 tested, would meet the stopping guideline. As each individual outcome is assumed to be Bernoulli-distributed and therefore distribution of all outcomes is binomial, a beta prior was chosen as this is the conjugate prior for the binomial distribution. The mean of the prior was fixed at 0.9, and the effective sample size of the prior was varied until a distribution was found such that there was a roughly 0.33 probability of a cure rate of less than 90%; roughly 0.33 probability was chosen as 4 out of 12 randomly assigned groups are expected to fail and therefore have a true cure rate of less than 90%. The prior chosen was beta (4.5, 0.5) with mean 0.9, variance 0.015 and a 0.34 probability of a cure rate of less than 90%. The relatively low precision of the prior will allow greater influence of the data in the posterior distribution. If the stopping guideline is met, sensitivity analyses using priors informed by observed cure rates in other randomly assigned groups or strata will be performed and will be provided to the DMC to help inform their decision to stop a group.

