**Fig. 2 Fig2:**
[figure not shown]
Initial probability of stopping groups over an estimated recruitment schedule for various true cure rates. The average true cure rate is uniformly distributed over 60–90%. Probabilities are calculated assuming no previous interim analysis. The total numbers of patients recruited at each month, of a total target of 1092, are 113 at 5 months, 153 at 6, 205 at 7, 257 at 8, 309 at 9, 361 at 10, 413 at 11, 465 at 12, 517 at 13, 569 at 14, 621 at 15, 673 at 16, 725 at 17, 777 at 18, 829 at 19, 881 at 20, 933 at 21, 985 at 22, 1037 at 23 and 1092 at 24. See Supplementary Figure 1, Additional file 1 for the cumulative probability of stopping a group.

Four analysis time points were chosen to provide multiple opportunities to detect failing groups while allowing adequate time between analyses for the accrual of patients and outcome data and preventing an unnecessary burden on time and resources needed for analyses and subsequent DMC meetings. The highest probability threshold (0.7) is determined by the maximum average cure rate of the genuinely inferior groups and by the recruitment schedule, as analyses need to be performed sufficiently early enough to gain the benefit of randomly assigning remaining patients to the other groups. The other thresholds (0.3, 0.5) were evenly spaced across the probabilities of stopping a group with an average cure rate, taking into consideration the first, early DMC meeting not based on these probabilities.

Therefore, considering the underlying projected recruitment, we expect the interim analyses to take place after 7, 10, 13 and 18 months. The number of patients in each group and the probability of stopping an inferior group of each strategy type at these analyses are listed in Table 4. By assessing the cumulative probability of stopping a group (Supplementary Fig. 1, Additional file 1), our schedule provides a balance between having more frequent meetings, which have a lower probability of stopping groups at any individual meeting but allow for earlier detection of poorly performing groups, and less frequent meetings, which have a higher probability of stopping a group but its low performance is detected later. The exception to this is having analyses every month but this schedule is impractical because of the resources required for an interim analysis.

**Table 4 Tab4:** Timing of interim analyses

	First	Second	Third	Fourth
Months since recruitment started	7	10	13	18

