### Limitations of the design

A potential weakness in the design is that the sample size was not originally calculated using Bayesian principles, but primary analyses will be conducted using Bayesian methods to allow for the calculation of posterior probabilities exploring the difference in cure rates between the interventions. However, for the non-inferiority comparisons, sample size estimates obtained using Bayesian methods are similar to or smaller than those obtained using frequentist methods [34], suggesting that our design is likely to be conservative. Additionally, secondary analyses will use frequentist methods for comparison. For interim analyses, the probability of correctly stopping a group, analogous to the frequentist concept of power, is determined by the true cure rate in the group and the number of analysed patients at each analysis and not by the overall group size.

The timing of and the number of patients at interim analyses are determined by at least one group, usually the 4-week treatment group with PEG-IFN since this has the shortest overall treatment duration, reaching a certain probability threshold of being stopped. This may mean delays in identifying unsuccessful groups receiving other strategies. This is unlikely if groups have cure rates lower than the average cure rate because, as discussed above, these will be detected faster than anticipated, but delays may occur if the cure rate is above the average but less than 90%. As the treatment length of patients in the RGT groups is unknown until after their day 7 visit, it is not possible to stagger treatment start dates so that the length between randomisation and EOT is the same for all strategies. Staggered treatment start might also lead to dropout after randomisation but before starting treatment, leading to inefficiency and potential bias. During the trial, cure rates will be monitored in all groups. If the cure rates are not as anticipated, either they are higher and lower than expected, and so our derived schedule is inappropriate based on these cure rates then the timing can be adjusted wih no penalty to the probability of incorrectly stopping recruitment into a randomised group, due to the use of Bayesian monitoring [22].

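### The 12% miss rate at 80% cure, the abstract's stopping probabilities and the claim that looks can be re-timed without penalty do not describe the four planned looks, which miss 44–54% of such groups

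*Protocol article*

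**What the plan says.** The rule (Monitoring) is that "recruitment into a group will stop if there is a greater than 0.95 posterior probability of the true cure rate being less than 90" (per cent), and "The prior chosen was beta (4.5, 0.5) with mean 0.9, variance 0.015". On the schedule, the article says "we expect the interim analyses to take place after 7, 10, 13 and 18 months". Table 4 puts 35 to 42 analysed patients per group at the last of these. Monthly looks are called impractical, and Alternative designs rejects a look after every outcome.

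Three sets of statements describe how the rule performs:

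- **Overall error rates** (Characteristics of Bayesian stopping guideline for individual groups): "For cure rates of more than 90%, the probability of incorrectly stopping a group is always maintained less than 0.05", and "The probability of incorrectly not stopping groups with cure rates of about 80% is 12" (per cent). The section likens correct and incorrect stopping to power and type I error, names no look schedule, and refers to a supplementary table.
- **Abstract, Results:** groups with cure rates below 60% "are very likely (>0.9 probability) to stop after about 25% of patients are recruited", and "Groups with moderately low cure rates (80%) are likely to stop (0.7 probability) before overall recruitment finishes".
- **Limitations of the design:** the look times can be changed with "no penalty to the probability of incorrectly stopping recruitment into a randomised group, due to the use of Bayesian monitoring".

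**The concern.** Table 3 itself casts doubt on the 12%. At 80% cure its minimum single-look stopping probability is 0.367 for 34–39 patients and 0.469 for 42–48, and no planned look goes beyond 42. Earlier looks add something, but hardly enough to reach 88%.

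These figures are the evidence that monitoring removes poor groups and spares good ones, and the article's conclusion that the operating characteristics are appropriate rests on them. A DMC taking them at face value would expect most groups at 80% cure to be stopped, and would think that looks can be moved freely. The article expects re-timing if recruitment or cure rates differ from projection, so that second belief would be acted on.

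**Working it through.** **Inputs.** Rule and prior from Monitoring; analysed patients per group from Table 4; full group size 78 from the note to Table 3.

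**Boundary.** At n patients, the smallest f with Pr(Beta(4.5 + n − f, 0.5 + f) < 0.9) > 0.95. This reproduces every boundary in Table 3. At n = 2, below the table's range, two failures of two suffice (posterior 0.954).

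**Cumulative stopping.** Start with all probability at zero failures. Between looks, convolve with Binomial(n_k − n_(k−1), 1 − cure rate). At each look, move the probability at or above the boundary to stopped. Simulation with 200,000 datasets agrees at 80% and 90% cure.

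| | PEG-IFN | RGT | Induction/maintenance |
|---|---|---|---|
| Looks (n) | 5, 14, 24, 42 | 3, 11, 21, 39 | 2, 8, 17, 35 |
| Failures needed | 3, 5, 6, 9 | 3, 4, 6, 8 | 2, 4, 5, 8 |
| Stop at 80% cure | 0.533 | 0.560 | 0.457 |
| **Miss at 80%** | **46.7%** | **44.0%** | **54.3%** |
| Stop at 90% | 4.6% | 5.25% | 4.4% |
| Stop at 91% | 2.9% | 3.3% | 2.9% |
| Stop at 60% by month 10 | 0.74 | 0.70 | 0.44 |
| Stop at 60% by month 13 | 0.96 | 0.92 | 0.88 |

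**Reproducing the 12%.** A fifth look at n = 78 still leaves a miss of about 17%, with 7.5–7.9% false stops at 90%. Frequent looks up to n = 78 come close:

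| Looks up to n = 78 | Miss at 80% | False stop at 90% | False stop at 91% |
|---|---|---|---|
| After every outcome | 12.4% | 14.2% | 9.4% |
| Every 2 patients | 13.0% | 13.2% | 8.6% |
| Every 5 patients (3, 8, … 78) | 13.6% | 11.7% | 7.3% |

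None of the schedules tried gives both a 12% miss at 80% and under 5% false stops just above 90%.

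**Abstract, 0.7 at 80% cure.** Table 3's row for 72–78 analysed patients gives 0.705, from one look at n = 72 with 13 failures needed. The last planned look has 35–42 patients.

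**Abstract, above 0.9 by about 25% recruited.** Table 3's row for 21–26 analysed patients gives 0.904 at 60% cure. As shares of a full group, 21/78 = 27% and 26/78 = 33%, but these patients are analysed, not merely recruited. Table 4 first shows a group at 21 or more at month 13, when 517/1092 = 47% are recruited. A quarter of recruitment is 273 patients, which Fig. 2 places between months 8 and 9. Only the month 7 look has then occurred. At 60% cure that look stops 0.4³ = 0.064 of RGT groups, 0.4² = 0.16 of induction/maintenance groups and, with at least 3 failures of 5, 0.317 of PEG-IFN groups.

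**Re-timing, false stops at 90% cure.**

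- PEG-IFN as planned, 5/14/24/42: 4.6%.
- Last look at 41 instead of 42, where the boundary falls from 9 failures to 8: 6.5%.
- 7/13/26/41, no look moved by more than two patients: 9.1%, and 6.2% at 91% cure.
- All shifts of at most four patients, across the three strategies: 2.5% to 9.2%.
- Monthly looks to month 18: 6.8–7.8%.

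**The case against.** Supplementary Table 1 is not available here and may state the schedule behind the 12%. The Methods also list the overall probability of stopping separately from the cumulative probability at specified time points, and Supplementary Fig. 1 is cited for the latter. The 12% may therefore be a correct figure missing its condition, not a miscalculation. That is fair, but the text gives it unconditionally.

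Four stronger readings are tempting and are not supported:

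- *That the claim of under 0.05 above 90% fails for this trial.* Under the planned looks it approximately holds: at most 3.3% at 91%, and RGT slightly over 5% only at about 90% itself. It fails only under the frequent looks needed to approach the 12%.
- *That only a look after every patient approaches 12%.* Looks every two or five patients give 13–14%.
- *That 0.7 at 80% cure is unattainable before recruitment ends.* Suppose outcomes after month 18 accrue at about 3.6 per group per month (an assumption; 52 recruited a month over 14 groups is 3.7 before losses). Groups would then have about 64, 61 and 57 outcomes at month 24. One added look there brings cumulative stopping at 80% to 0.66–0.74. The article calls its last look flexible, but Table 4 has no such look.
- *That re-timing always raises false stops.* It can also lower them.

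The abstract also speaks of cure rates below 60%. At 50%, stopping by month 10 (33% recruited) is 0.92, 0.89 and 0.66, so only PEG-IFN passes 0.9 even then.

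On re-timing, the Bayesian defence is partly right. The posterior from given data does not depend on when looks occur. Averaged over the prior, the chance that a stopped group truly has at least 90% cure stays below 0.05 on the schedules checked (1.4–3.5%). But the sentence concerns the probability of incorrect stopping, which the article itself treats as analogous to type I error.

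**Conclusion.** The point holds for the 12% miss rate, the two abstract figures and the re-timing statement. The planned looks miss 44–54% of groups at 80% cure, roughly four times the stated rate. They stop 0.46–0.56 of such groups by the last look, against 0.7 in the abstract, and at 60% cure they reach 0.88–0.96 at 47% recruited, not about 25%. False stops at exactly 90% cure are 4.4–5.3% as planned, and move between 2.5% and 9.2% with shifts of at most four patients.

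This rests on the Table 4 patient numbers, independent outcomes with one cure rate across genotype strata, and the guideline being followed whenever met, although the DMC has discretion. The near-continuous schedule behind the 12% is inferred from the match, not stated. A reader might infer that the guideline is unsound. The article does not support that: it deliberately tolerates missing groups just below 90%. What needs correcting is the description of performance.

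**What to change.** 1. State the look schedule behind the 12%, or remove the figure.
2. In the results section and the abstract, give exact cumulative stopping probabilities for the four Table 4 looks, by strategy and true cure rate (at least 60%, 80%, 90% and 91%). In the abstract, distinguish analysed from recruited patients.
3. Qualify the re-timing sentence: the posterior interpretation is unaffected, but the probability of stopping a group at a given true cure rate changes with the number and timing of looks.
4. Recompute the cumulative false-stop probability and give it to the DMC whenever a look is added or moved.

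The cost is a short calculation, some redrafting and less favourable stated figures. The stopping guideline, prior and sample size need not change.

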Another approach would be to analyse the outcome data after every reported outcome rather than at scheduled interim analyses, which could reduce the time until a genuinely inferior group is stopped. Implementing this would be complex because of the many groups and varying treatment lengths. The small benefit in the reduction in time would not justify the additional work required to monitor outcomes intensely.

In VIETNARMS, if a group performs badly, then randomisation into that group will completely stop. Alternatively, the trial could have used response-adaptive randomisation where all groups would be retained but the allocation ratio would alter to favour randomisation into a group that is showing the most potential. For several reasons, this design was not considered suitable for VIETNARMS. First, each group will be tested separately and, as the randomisation is factorial, each group is the result of multiple randomisations and so it could be unclear how to adapt the randomisation allocations correctly. For example, the ribavirin groups may perform better with one shortening strategy but much worse with another strategy; in this case, it is unclear how the ribavirin randomisation allocation should be changed. Second, if a group is performing particularly badly and there is no prospect of that strategy being adopted, then continuing with that group would be a burden on resources, including on the number of patients enrolled. Third, in an open-label trial such as VIETNARMS, response-adaptive randomisation risks unblinding investigators to the relative performance of open groups, information that is usually privy only to a DMC.

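### The stated 12% chance of missing an 80%-cure group is not what the four planned interim looks deliver; on Table 4's counts they miss 44–54%

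*Protocol article*

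**What the plan says.** The rule and prior are fully specified in the Monitoring section: "recruitment into a group will stop if there is a greater than 0.95 posterior probability of the true cure rate being less than 90"%, and "The prior chosen was beta (4.5, 0.5) with mean 0.9, variance 0.015". Table 4 schedules four looks, at months 7, 10, 13 and 18. By the fourth, 42, 39 and 35 outcomes are expected per PEG-IFN, RGT and induction/maintenance group. The note to Table 3 gives the full group size: "Groups will recruit a minimum of 78 patients with 39 patients in each stratum".

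The section on the characteristics of the stopping guideline then gives overall stopping probabilities, described as the analogues of power and type I error and referred to Supplementary Table 1:

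- On missed stops in moderately poor groups: "The probability of incorrectly not stopping groups with cure rates of about 80% is 12"%
- On false stops in good groups: "For cure rates of more than 90%, the probability of incorrectly stopping a group is always maintained less than 0.05"
- On very poor groups: "almost all groups are stopped when the true cure rate is not more than 70"%

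That text does not say which looks these figures assume. The abstract adds: "Groups with moderately low cure rates (80%) are likely to stop (0.7 probability) before overall recruitment finishes". Under Alternative designs, continuous review is described and turned down: "Another approach would be to analyse the outcome data after every reported outcome rather than at scheduled interim analyses". The section on timing also calls monthly analyses impractical.

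**The concern.** An overall stopping probability depends on how often, and at what counts, the rule is applied. More looks raise the chance of stopping a poor group and also the chance of stopping a good one, so the two error rates mean something only when they come from one named schedule. Here the false-stop figure fits the four planned looks, while the missed-stop figure fits review of the whole group of 78 outcomes.

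The conclusion that the operating characteristics are appropriate rests on these figures. If the 12% does not belong to the planned monitoring, the guideline's ability to detect an 80%-cure group is substantially overstated.

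**Working it through.** **Inputs.** Rule and prior: Monitoring. Full group size of 78: Table 3 note. Look counts: Table 4. Recruitment by month: Fig. 2 caption.

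**Boundary.** After n outcomes with f failures the posterior is beta(4.5 + n − f, 0.5 + f). The boundary b(n) is the smallest f with Pr(cure < 0.9) > 0.95. At n = 42, f = 8 gives 0.944 and f = 9 gives 0.977, so b = 9. At n = 41, f = 8 gives 0.95005, so b = 8. Every failure count in Table 3 is reproduced. At n = 2, below Table 3's range, two failures give 0.954 and the group stops. This agrees with Table 4's 0.070: (0.4³ − 0.1³)/(3 × 0.3) = 0.063/0.9 = 0.070.

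**Cumulative probability.** Let q = 1 − cure rate. Between looks, new failures are Binomial(n_k − n_(k−1), q). At each look, convolve this with the distribution of failures among groups still open, record the mass at or above b(n_k) as stopped, remove it and continue. P(stop) is the sum of the removed mass. The calculation is exact.

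**Reproducing the stated 12%.** Reviewing after every outcome to n = 78 gives P(stop at 80%) = 0.876, so 12.4% are missed. False stops on that schedule are 0.138–0.142 at 90%, 0.090–0.094 at 91% and 0.055–0.059 at 92%. They fall below 0.05 only from about 92.2–92.3%. (Ranges: starting at n = 3 or n = 1.)

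**The four planned looks, at 80% cure.**

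- PEG-IFN, n = 5/14/24/42, b = 3/5/6/9: 0.058 + 0.095 + 0.211 + 0.169 = 0.533
- RGT, n = 3/11/21/39, b = 3/4/6/8: 0.008 + 0.155 + 0.115 + 0.283 = 0.561
- Induction/maintenance, n = 2/8/17/35, b = 2/4/5/8: 0.040 + 0.043 + 0.180 + 0.194 = 0.457

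| Schedule | Stop at 80% | Missed at 80% | Stop at 70% | False stop at 90% | False stop at 91% |
|---|---|---|---|---|---|
| Four looks, PEG-IFN | 0.533 | 46.7% | 0.935 | 0.046 | 0.029 |
| Same, fourth look at 41 | 0.621 | 37.9% | 0.959 | 0.065 | 0.041 |
| Four looks, RGT | 0.561 | 43.9% | 0.939 | 0.0525 | 0.033 |
| Four looks, induction/maintenance | 0.457 | 54.3% | 0.886 | 0.044 | 0.029 |
| Four looks plus n = 78 (Table 4 counts) | 0.83 | 17% | 0.998 | 0.075–0.079 | 0.043–0.046 |
| Every outcome to 78 | 0.876 | 12.4% | 0.999 | 0.138–0.142 | 0.090–0.094 |

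Even review after every outcome as far as n = 42, the largest count at the fourth look, stops an 80% group with probability only 0.67, a 33% miss.

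**Table 4's PEG-IFN entry.** Averaging over cure rates uniform on 60–90%, n = 42 with b = 9 gives 0.635, not the printed 0.710. With n = 41 and b = 8 the average is 0.696. With n = 42 and a boundary of 8, which Table 3 does not allow at 42, it is 0.710. On that last reading P(stop at 80%) is 0.646 (35% missed) and false stops at 90% are 0.070. The entry must be reconciled before final figures are printed, but no reading approaches a 12% miss.

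**The abstract's 0.7.** Assume lags from randomisation to outcome of 16, 20 and 24 weeks (4, 8 and 12 weeks of treatment plus 12). Outcomes available at month 24 then come from patients recruited by about months 20.3, 19.4 and 18.5. That is roughly 897, 850 and 803 patients, or 64, 61 and 57 per group after dividing by 14. The four looks plus one at those counts give P(stop at 80%) = 0.70, 0.74 and 0.66. The 0.7 is therefore attainable with a look at the end of recruitment, but Table 4 schedules none after month 18.

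**The case against.** **The basis is not visible.** Supplementary Table 1 is not shown, so its schedule, cure-rate grid and maximum count are unknown. If its only value above 90% is 95%, as in Table 3, even every-outcome review gives about 0.01 there and the false-stop statement holds on that grid. This stands as a limit: how the 12% was produced is inferred from a numerical match. It does not rescue the 12% as a property of the planned looks.

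**No schedule can give both figures.** A reader might infer this, and the documents do not support it. The text says about 80%. The four planned looks plus one at n = 78 miss 12.0–12.4% at 79%, with false stops of 0.043–0.046 at 91%. On a whole-percent grid both figures are met. The fit is still imperfect: at exactly 80% the miss is 17%, at 90.5% false stops are 0.057–0.061, and the look at 78 is not planned. Reviews every two to five outcomes to 78 miss 13–14%, so every-outcome review is not the only near match either.

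**The abstract's 0.7 is impossible before recruitment closes.** It resembles Table 3's single-look 0.705 for 72–78 patients, which might suggest this. The month-24 calculation shows otherwise.

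**Timing is flexible.** The article lets groups stop at any time and calls the last analysis the most flexible. That is fair, but extra looks raise both probabilities, so the quoted pair still needs a named schedule.

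**The committee would be misled.** One might say an unstopped group would be read as having passed an 88%-sensitive screen. Nothing in the article shows this. The committee works from posterior probabilities of observed data, Table 3 shows modest single-look figures at 80% (0.367 at its minimum for 34–39 patients, 0.469 for 42–48), and the final analysis is comparative.

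**Conclusion.** The point holds: the overall operating characteristics are wrong as a description of the planned monitoring. On the four scheduled looks with Table 4's counts, the missed-stop probability at 80% cure is 44–54% rather than 12%. It is 38% for PEG-IFN if its fourth count is 41. At 70% cure 0.89–0.94 are stopped (0.96 for PEG-IFN at 41), which is weaker than almost all. The false-stop claim above 90% is close to right on those looks: 0.044–0.0525 at exactly 90% and about 0.03 at 91%. With a PEG-IFN count of 41 it is 0.065 at 90% and 0.041 at 91%.

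These results assume Table 4's projected counts, independent outcomes with a common cure rate within a group, monitoring on combined strata, and a group closed whenever the guideline is met.

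**What to change.** 1. State the schedule of looks, maximum count and cure-rate grid behind Supplementary Table 1.
2. Reconcile Table 4's fourth-look PEG-IFN count and probability with Table 3's boundary.
3. Recompute missed-stop and false-stop probabilities on the four planned looks, by strategy, and print them side by side in the section on the stopping guideline. With the present counts these are 44–54% missed at 80%, 0.89–0.94 stopped at 70%, and 0.044–0.0525 false stops at 90%; the PEG-IFN values depend on step 2.
4. If every-outcome or full-group (n = 78) figures are kept, label them as such and show their false-stop rates beside them: about 14% at 90% and 9% at 91% for every-outcome review, and 7.5–7.9% at 90% for four looks plus 78.
5. In the abstract, either say that 0.7 assumes a look near the end of recruitment that is not scheduled, or give the planned-look value: 0.46–0.56, or 0.62 for PEG-IFN at 41.

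The cost is one rerun of an existing calculation and some rewording. It needs no extra patients and no change to the rule. The reported sensitivity becomes less favourable.
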